To this end, our UCLA scientists are working in close collaboration with the City of Los Angeles (L.A.) Department of Aging (DoA), a local Area Agency on Aging (AAA) overseen by the U.S. Administration for Community Living (ACL), to design, implement and test an effective sustainable program to increase physical activity and decrease stroke risk. Federal congressionally mandated Title III funds are distributed each year to AAAs that use this money to contract with local service providers (including a vast network of senior centers) to provide services to 3 million seniors annually [18]. These services include but are not limited to assistance with meals, transportation, housing, safety and, increasingly, health promotion. Under the leadership of [name], the U.S. ACL has advocated for the local AAAs to implement evidence-based health promotion programs such as the Chronic Disease Self- Management Program developed at Stanford University [19]; under the leadership of our collaborator General Manager [name], the City of L.A. DoA has been a national leader in this effort to implement evidence-based programs.

Our team is currently testing the effectiveness of a culturally-tailored walking intervention called “Worth the Walk” (WTW) developed for African American, Latino, Chinese and Korean seniors on reducing physical inactivity. Our primary specific aim is: 1) to measure the effectiveness of the intervention in increasing walking levels (mean steps/day measured by pedometers) at the end of the 4 week intervention, and persistence after two months. We hypothesize that WTW will increase physical activity by increasing knowledge about stroke risk factors and improving self-efficacy for reducing stroke risk and being physically active. In addition to the primary study aim, the study has two sub-aims: 2) to explore the relationship between the intervention and biological markers of health including blood pressure, body-mass index, non-HDL cholesterol, glycosylated hemoglobin (HgA1c), and c-reactive protein (CRP); and 3) to examine the relationship between the intervention, self-efficacy, and healthcare seeking behaviors in order to best control stroke risk factors.

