### Study procedures

#### Recruitment, screening, enrollment, baseline

Recruitment takes place at the same 4 senior centers (one for each ethnic group) where in-house WTW case managers have been trained. Members of the research team make brief presentations describing the project during events attended by large numbers of seniors, such as the low-cost hot midday meals provided at all of the senior centers participating in this study. Recruitment flyers our team developed in partnership with our mini-CABs listing the study objectives, eligibility criteria, and staff contact information are also posted and distributed at senior center sites. Potentially eligible seniors are invited to approach/contact study staff individually to be formally screened on pre-determined days at the senior center.

During screening, study staff complete in face-to-face format a screener form listing the eligibility criteria with each prospective participant. Prospective participants are given a FITBIT® Zip pedometer and instructed on its proper use. A letter and reply form (referenced above) is then faxed to the physician indicated by each potentially eligible participant (along with the patient’s signature indicating consent for our staff to contact the physician) describing the intervention and asking him or her to contact the study team within one week stating whether his or her patient has any medical contraindication to participating, including unstable angina, uncompensated heart failure, uncontrolled cardiac arrhythmia, severe aortic stenosis, hypertrophic cardiomyopathy, cardiomyopathy from recent myocarditis, severe pulmonary hypertension, abdominal aortic aneurysm, recent systemic or pulmonary embolus, thrombophlebitis, and severe balance problems. A faxable reply form is provided so that the physician can simply check “yes” or “no.”

Approximately one week after screening has been completed, eligible participants are invited to attend a baseline data collection session at the senior center, during which trained project staff complete the informed consent process with each potential participant individually in a private setting. After participants have provided written documentation of informed consent, staff proceed to collect baseline data (see Table 1).

**Table 1 Tab1:** Data collection measurements

Construct	Measurement	When measured			Source
Primary outcomes					
Walking level	Mean steps/day over 1 week	T0	T1	T2	Pedometer

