Physical activity	International Physical Activity Questionnaire (IPAQ)	T0	T1	T2	Survey
Stroke and stroke risk factor knowledge	Stroke Action Survey (STAT)	T0	T1	T2	Survey
	Stroke risk factor knowledge				
Self-efficacy	General Self-Efficacy Scale	T0	T1	T2	Survey
	Chronic Disease Self-Efficacy Scale				
	Outcome Expectations for Exercise Scale (OEE)				
Secondary/exploratory outcomes					
Blood pressure	Universal data collection protocol	T0	T1	T2	Physical exam
BMI (kg/m2)	Universal data collection protocol	T0	T1	T2	Physical exam
Non-HDL cholesterol	Point-of-care CardioChek meter	T0		T2	Fingerprick
HDL cholesterol	Point-of-care CardioChek meter	T0		T2	Fingerprick
Triglycerides	Point-of-care CardioChek meter	T0		T2	Fingerprick
Glycosylated hemoglobin (HgA1c)	Dried blood spots	T0		T2	Fingerprick
c-reactive protein (CRP)	Dried blood spots	T0		T2	Fingerprick
Healthcare seeking	Visits with healthcare provider	T0		T2	Survey
Restricted bed days	Restricted activity	T0		T2	Survey
Social support/network	Interpersonal Support Evaluation List (ISEL)	T0	T1	T2	Survey
Health-related quality of life	Medical Outcomes Study SF-12	T0	T1	T2	Survey
Depressive symptoms	Patient Health Questionnaire (PHQ-9)	T0	T1	T2	Survey
Disability	ADL Summary Scale	T0	T1	T2	Survey
Risk perception and worry	SPRITE survey items	T0	T1	T2	Survey
Trust in physicians	Trust in Physicians Scale	T0	T1	T2	Survey
Trust in medical researchers	Trust in Medical Researchers	T0	T1	T2	Survey
Sleep	MOS-Sleep Scale	T0	T1	T2	Survey
Stress	Perceived Stress Scale-4 item	T0	T1	T2	Survey
Aging expectations	Expectations Regarding Aging (ERA-12)	T0	T1	T2	Survey
Other measures^a^					
Demographics/SES	REDCap database questions on demographics/highest completed education	T0			Survey
Acculturation^b^	Vancouver Index of Acculturation (VIA)	T0			Survey
Medical comorbidities	Katz/Charlson Comorbidity Index	T0			Survey
Neighborhood walkability	Neighborhood Environment Walkability Scale-Abridged (NEWS-A)	T0			Survey
Smoking	NHANES survey items	T0			Survey

*T0* baseline, *T1* 30 day follow-up, *T2* 90 day follow-up

^a^ These constructs, though not linked explicitly to specific aims, are considered to be critical covariates, likely to be associated with outcomes, which will be measured to evaluate the success of the randomization

^b^ Measured for non-African American participants only

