### Sample size and power

As described above, our primary outcome of interest is change in mean steps/day, while our main secondary outcome measure is change in systolic blood pressure. Based on our capacity, we plan to enroll 240 subjects from 4 senior centers. From our previous senior center research we estimate that as many as 15 % of subjects will not complete follow-up. Data from our previous senior center studies of older Latinos and African Americans showed mean steps/day 2713 (std. dev. 2190) and mean SBP 141 mm Hg (std. dev. 20 mm Hg); intra-class correlation within senior centers was at 0.0085. Since we propose a repeated measures design with 3 repeated measurements [46], the underlying statistical power of the study comes from two dimensions of observations: the number of unique subjects and the number of repeated measurements within a subject. Based on sample size/power analytic methods for repeated measures analysis [47, 48], using a 2-sided test with a type I error of 0.05, and a type II error of 0.2 (power 80 %), and assuming an average 2.7 data points per subject and an auto-correlation at 0.2 level, after adjusting for clustering, the effective sample size will be 96 subjects in each arm, which will enable us to detect effect sizes as small as 581 steps/day (far below a clinically meaningful increase of 5000 steps/day [49]) and 5.3 mm Hg. A decrease of 5 mm Hg substantially decreases stroke risk [50] and is comparable to effect sizes observed in walking interventions of similar intensity [51].

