#### Comparing baseline characteristics of intervention and control arm subjects

Using t-tests for continuous variables and chi-square tests for categorical variables, we will compare the two groups on baseline characteristics to measure the success of the randomization: 1) sociodemographic characteristics; 2) mean steps/day over 1 week in the window post screening and distribution of pedometers, to the T0 baseline data collection one week later; 3) systolic blood pressure, body mass index, non-HDL cholesterol, HgA1c; 4) stroke knowledge, self-efficacy. Since steps/day is a continuous variable, at each time-point (30 days/T1 and 90 days/T2) we will perform a simple descriptive cross-sectional analysis of mean change in scores between baseline and follow-up in each treatment arm. In our primary analyses, we will test the statistical significance of the unadjusted difference in change-scores between the groups using t-tests for symmetrically distributed data and analogous nonparametric tests such as the Wilcoxon sign rank tests for data that are skewed. Imbalance between the treatment arms of characteristics described above would inflate the standard error, making the unadjusted analyses appropriately conservative; therefore, the unadjusted analyses will serve as the primary results of the trial. If, however, we did identify chance differences between the treatment arms in the distribution of the baseline level of the outcome, then we will also conduct secondary analyses in which we will use multivariate modeling, such as analysis of covariance, to adjust for these factors. The adjusted means of the change-scores from multivariate models will be compared and tested between the two arms, and will also be compared with the unadjusted means to assess the influence of these factors on endpoints. As sensitivity analyses, we will also examine the difference between groups in the absolute steps/day (instead of the change-score), adjusting for baseline. These sensitivity analyses will allow us to compare outcomes between groups without assuming linearity of effect across different baseline levels of physical activity. Using multivariate modeling, we will also test interactions between treatment arm and selected effect modifiers (e.g., age, level of acculturation, etc.) to identify sub-groups of participants who improve more than other groups. Since this trial is not designed with power to examine these subgroups, these analyses will be exploratory and hypothesis-generating in nature. Finally, we will assess changes in steps/day between baseline and the end of the intervention period, and differences between the control and intervention groups in steps/day trajectories over time. These analyses will consist of graphical analysis and parametric statistical testing using repeated measures mixed effects models [55, 56]. To determine the extent to which increases in stroke knowledge and self-efficacy mediate improvements in steps/day, the variation (R-squared) in increase in steps/day is explained by variation in increase in the stroke knowledge and self-efficacy constructs will be calculated [57, 58]. Analysis of the effect of the intervention on all the secondary and exploratory outcomes will follow the same analysis.

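### The R-squared planned to measure mediation by stroke knowledge and self-efficacy measures association between changes, not how much of the intervention effect passes through them

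*Protocol article*

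**What the plan says.** The Background of the protocol article makes the mechanism part of the trial's hypothesis: "We hypothesize that WTW will increase physical activity by increasing knowledge about stroke risk factors and improving self-efficacy for reducing stroke risk". The mediation analysis appears once, near the end of the section on comparing baseline characteristics, under Statistical analyses. Its purpose is "To determine the extent to which increases in stroke knowledge and self-efficacy mediate improvements in steps/day". The statistic follows in the same sentence: "the variation (R-squared) in increase in steps/day is explained by variation in increase in the stroke knowledge and self-efficacy constructs will be calculated". Two references are cited there. No other mediation method appears in the article.

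Table 1 puts the outcome and the mediators on one schedule, with rows such as "Mean steps/day over 1 week T0 T1 T2" and "General Self-Efficacy Scale T0 T1 T2"; the stroke knowledge survey is also taken at all three visits. The Abstract and Table 1 list knowledge and self-efficacy among the primary outcomes. They are therefore also compared between arms in their own right, under the Overview of analytic plan and with the adjustment described under Multiple comparisons.

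**The concern.** Mediation has two links: the arm must move the mediator, and the mediator must move steps/day. The mediated effect is their product. The planned R-squared uses neither the arm nor that product. It could be computed with the allocation column deleted, or in a cohort that received no intervention.

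Knowledge or self-efficacy and walking could change together for reasons that are not mediation, and the article itself describes two. Its account of the intervention expects participants to feel reinforced when they meet their walking goals, so walking may raise self-efficacy. Its Discussion concedes that unblinded participants may improve because they know their arm, which could shift survey answers and steps together. The article does not show how strong either route is.

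At stake is the account of why the programme works, in a trial meant to lead to wider use of a fixed curriculum.

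**Working it through.** The article gives no figure for the mediation analysis. Its detectable effect is used here only to set the scale.

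**1. The plan's own figure** (Sample size and power). One reconstruction gives 120 / (1 + 29 × 0.0085) = 96.3 effective participants per arm, taking 30 per arm per centre. The mean of three measurements with first-order autoregressive correlation 0.2 has variance factor (3 + 2 × 0.44) / 9 = 0.4311. The detectable difference is then (1.960 + 0.842) × 2190 × √(2/96 × 0.4311) = 581 steps/day, as stated. On the stated SD this is d = 581 / 2190 = 0.265.

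**2. Model.** One mediator stands in for the constructs. Arm X is 0 or 1 in equal numbers. Mediator change is M = aX + e1, and steps change is Y = cX + bM + e2. The residuals have SD 1 and correlation ρ. The true indirect effect is a × b. The planned statistic is R² = cov(M,Y)² / (var M × var Y). The values of a, b and ρ are assumptions; the article gives none. Each case was also simulated with 204 participants (240 less the article's 15 % loss, 240 × 0.85) and 4,000 replicates.

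**3. No mediation, arm does not move the mediator** (a = 0, b = 0, c = 0.265). R² = ρ² / (1 + d²/4), with d²/4 = 0.0176.

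| ρ | Formula | Simulated mean R² | True indirect effect |
|---|---|---|---|
| 0.3 | 0.09 / 1.0176 = 0.088 | 0.092 | 0 |
| 0.5 | 0.25 / 1.0176 = 0.246 | 0.247 | 0 |
| 0.7 | 0.49 / 1.0176 = 0.482 | 0.481 | 0 |

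**4. No mediation, arm does move the mediator** (a = 1, b = 0, c = 0.265, ρ = 0.5). The covariance is 0.5 + 1 × 0.265/4 = 0.566, so R² = 0.566² / (1.25 × 1.0176) = 0.252 (simulated 0.253). The true indirect effect is 0.

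**5. Full mediation** (c = 0, a × b = 0.265, ρ = 0). R² = (b² + d²/4) / (1 + b² + d²/4).
- a = 1, b = 0.265: (0.0704 + 0.0176) / 1.0880 = 0.081 (simulated 0.085).
- a = 0.5, b = 0.531: (0.2815 + 0.0176) / 1.2991 = 0.230 (simulated 0.232).

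Here 0.265 is in units of the residual SD of steps change given the mediator. In units of the whole within-arm SD, the denominator is 1.0176 and the values are 0.086 and 0.294. The overlap with steps 3 and 4 remains.

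**6. A case where R² stays small.** With a = 1, b = 0, c = 0.265 and ρ = 0, the simulated mean is 0.008. R² is not always large when mediation is zero.

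**7. Comparison.** Steps 4 and 5 can share the same arm effect on the mediator (a = 1). R² is then 0.25 with no mediation and 0.08 with full mediation, so it does not even order the two correctly.

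**The case against.** The strongest reply is that the first link is in the plan: knowledge and self-efficacy are outcomes and will be compared between arms. A reader might infer from the mediation sentence that the arm's effect on the mediators is never examined. The article does not support that, and in the cases of step 3 the planned comparison would estimate the missing effect. This part stands, but it does not rescue the R-squared. Step 4 shows a clear arm effect on the mediator, a sizeable R-squared and no mediation. Two separate results do not add up to a mediated effect.

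A second reply is that this is a condensed article whose cited methods are not at hand, and that model terms may be left to the analysis plan. That is fair for covariates and timing. The choice of statistic, however, is made in the article, and it does not match the purpose given in the same sentence.

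Third, R-squared is large under zero mediation only in some settings. This stands: step 6 gives 0.008, and the correlations are assumed. The point is only that it can be large.

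**Conclusion.** The point holds: as written, the planned R-squared measures association between changes and cannot show how much of the intervention effect runs through knowledge and self-efficacy. Under the assumed values it is about 0.09 to 0.48 with no mediation and about 0.08 to 0.23 with full mediation of a 0.265 SD effect. These ranges rest on a single mediator, a linear model and chosen correlations. The missing arm term does not depend on them.

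Four stronger readings are not supported.
- A reader might infer that changes over the same interval will be paired. The common schedule makes this natural, but the text does not say so, and lagged pairing would still leave out the arm.
- A reader might infer that the mechanism hypothesis will be accepted or rejected on this number. The article sets no threshold or test for it; the analysis is supportive.
- A reader might infer that full mediation would look negligible because arm explains only 0.0176 / 1.0176 = 1.7 % of the variance in steps change. That is the variance explained by arm, whereas the plan calculates the variance explained by the mediators, which step 5 puts at about 8 to 23 %.
- A reader might infer that the main result is at risk. Change in steps/day is the primary endpoint, and its between-arm comparison does not use this analysis.

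**What to change.** Replace the R-squared sentence with an indirect-effect analysis on data already scheduled:
- the arm effect on each mediator at T1, adjusted for its baseline value;
- the effect of the T1 mediator on steps/day at T2, in a model with arm, baseline steps, baseline mediator, site and gender (the last two are the randomisation strata);
- the indirect effect as the product of the two, with a bootstrap interval;
- a sensitivity analysis for unmeasured mediator-outcome confounding.

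The last item is needed because the product is not immune. In the setting of step 4 the simple product averaged 0.50 when the truth was 0. Taking the mediator before the outcome does not remove this either, since walking already changed by T1 could drive both T1 self-efficacy and T2 steps.

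The smaller alternative is to keep the R-squared, call it the association between changes, and drop the claim that it measures mediation.

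The cost is wording and modest programming, with no new data. The downside is wide intervals at this sample size and reliance on the assumption of no unmeasured confounding, which should be stated with the result.

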
### Process evaluation

We will examine the variation in effectiveness of the intervention among the 4 sites and will conduct a formal process evaluation to: 1) determine general and site-specific factors associated with greater effectiveness; 2) assess the feasibility, acceptability, and sustainability of the intervention; 3) measure the costs needed to implement and maintain the intervention. We will meet separately with key stakeholders at each site including seniors (RCT participants), case manager group leaders, senior center directors, other senior center staff involved in implementing the program (for example the staff members who set the schedules at the senior centers), and 2–3 healthcare providers involved in the enrollment screening process for participants at each site. In semi-structured interviews guided by previous successful implementation analyses [59, 60] we will ask questions such as: What was your role in the intervention and what outcomes did you seek to achieve? How was the intervention received by you and others in your site and did this change over time? What are the potential barriers and facilitators to implementing the intervention outside of the research study? What problems were associated with delivering the intervention and how might they translate (or not) into “real-world” implementation beyond the study trial (NIH grant) period? How did this program affect workload, burden and space? What potential modifications to the intervention could be made to maximize implementation? How (if at all) did this program change your relationship with the healthcare/senior center community? Transcripts will be read by 2 investigators who will use previously-described content analysis methods [60, 61] to identify behaviors, attitudes, personal characteristics, contexts, processes, and policies the informants believed to be associated with the implementation and sustainability of the intervention. Start-up costs needed to implement the intervention (such as items required for group leader training) will be tracked and recorded.

## Discussion

Results from this trial will provide important insight into the design and effectiveness of sustainable community-based interventions aiming to reduce stroke risk and mitigate disparities among hypertensive ethnic minority seniors. We have combined two different theories from motivational psychology with an extensive body of stroke education using materials from the AHA/ASA to develop a culturally-tailored intervention that has been directly integrated into the aging services network in Los Angeles. The demographic composition of Los Angeles is representative of projected trends for the nation; therefore, culturally-tailored projects that succeed in Los Angeles are natural models to take to scale nationally.

We recognize that a major disadvantage to using a wait-list control rather than an active simultaneous control is that participants are not blinded to whether or not they are receiving the intervention and thus may have different expectations of improvement during the data collection period. In other words, participants in the intervention arm might improve just because they know they are in the intervention arm rather than from the content of the intervention (and conversely those on the wait list might show little improvement because they know they are not “supposed” to improve while on the wait list). In addition, there could be disproportionate follow-up between study arms as wait-list participants move away or lose interest that could bias the study findings. Alternatively, participants randomized to the wait list control arm could seek their own plan to prevent stroke risk outside of the intervention, contaminating the control arm.

Nevertheless, given the strong level of enthusiasm by senior center leaders and clients (seniors) for this type of intervention, it is not feasible to have a blinded control arm within a single senior center; this would be perceived as unfair and generating ill-will among the senior center attendees. To minimize the effect of non-blinding on the study design, we ensure that all participants receive the same frequency of contact from study staff in terms of phone call reminders and incentives including pedometers.

Though multifaceted (including both formal stroke education and behavioral change strategies), this intervention is intentionally designed to be low-cost, sustainable and scalable. We chose to use in-house AAA-funded case managers rather than professional healthcare providers because a major goal of this project is to evaluate a practical and sustainable intervention that can be scaled up across the national aging services network; thus, even a modest stroke risk factor reduction in physical activity or blood pressure could have a tremendous population impact on preventing strokes and decreasing stroke disparities. Upon completion of this trial, we will have trained a cadre of senior-center based case managers in a new skill set of health disparities intervention implementation that can be used not only for stroke risk factor reduction interventions but also other evidence-based health promotion programs.

